**Lay Summary of Research**

Obesity is becoming more common in the UK and already affects ~24% of the population. Common health problems associated with obesity include heart disease, diabetes and mobility problems, all of which can significantly impact on the quality of life of those affected. Surgical and drug treatments for obesity are now being used more frequently, and there is little evidence comparing one treatment with another and very little is know about the long term effects of treatment (e.g. over several years). We aim to combine two UK primary care databases – the GPRD and QRESEARCH, and conduct a cohort study to assess the effect of treatments on a range of outcomes including mortality, post-operative complications, type 2 diabetes, cardiovascular disease, fractures, cancer, fatty liver, acute liver injury, obstructive sleep apnoea, weight, body mass index and blood lipid profile. We will compare the occurrence of these outcomes in obese people who receive weight loss surgery, obese people who receive weight loss medication, and obese people who receive no treatment. The results of this study will improve the evidence base available to doctors and patients trying to decide the best treatment options for people with obesity.

**Objectives**

To measure long term major clinical outcomes in people who have had bariatric surgery and compare them with a) people receiving pharmaceutical treatment for obesity and b) obese people receiving no treatment.

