**Study Type**

This is a hypothesis testing study; throughout the null hypothesis will be that there is no clinical difference in outcomes following bariatric surgery or pharmacological treatment for obesity, compared with receiving no treatment.

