**Study Design and Study Population**

A combination of two UK databases offers an excellent opportunity to study the clinical effects of interventions for obesity; the UK General Practice Research Database (GPRD) and QRESEARCH. In combination the GPRD and QRESEARCH contain information from >1100 UK general practices, and have current and historical data for >20 million patients. Continuous patient records include details of all consultations, diagnoses, prescribed medicines and basic demographic data. Patients are representative of the England & Wales population in terms of age, sex and geographical distribution [refs]. Data quality is subject to rigorous checks and audits and >500 peer reviewed studies have been published using GPRD or QRESEARCH data including studies investigating unintended effects of medication (GPRD, 2010; QRESEARCH, 2010). GPRD and QRESEARCH draw information from mutually exclusive practices and are therefore fully complementary.

*3.1 Study Design - Patient population, exposures of interest, inclusion/exclusion criteria*

The cohorts will comprise obese patients registered in the GPRD and QRESEARCH:

- Eligible patients will be those aged 18+ years with at least 12 months research standard registration time in the GPRD or QRESEARCH AND with one of the following exposures recorded by the study start:
  - A record of bariatric surgery with at least 12 months prior registration to ensure incident status (specific type of bariatric surgery used will be determined using data recorded in patient records); OR
  - A first prescription for orlistat with at least 12 months prior registration to ensure incident usage; OR:
  - A record of BMI>30 with neither bariatric surgery nor a prescription for orlistat – these patients will act as the **comparison group**
- The date of surgery or first orlistat prescription will be termed the index date. Each patient with surgery or orlistat will be matched with up to 5 obese patients without a record of these treatments, on age (within 5 years), sex and practice with at least 12 months research standard registration prior to the relevant index date.
- Patients will be followed until the earliest of; an outcome of interest, death, transfer out of the practice or last data collection date.

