**Statistical Analysis and Covariates**

*Baseline Comparisons*

We will use baseline data to compare the background characteristics of patients receiving surgical and pharmacological interventions for obesity with those receiving no intervention. This will give a broad picture of how these interventions are being targeted in the UK as a whole. Odds ratios and 95% confidence intervals will allow us to determine statistically and clinically relevant differences, using patients with no intervention as the baseline group. As a subgroup analysis, differences in the targeting of specific forms of bariatric surgery will also be determined. **Covariates** to be assessed will include age, sex, weight, BMI, smoking status, alcohol consumption and a range of co-morbidities such as coronary heart disease, hypertension and diabetes.

*Cohort analysis*

We will compare outcomes between patients receiving surgical and pharmacological interventions for obesity with those receiving no intervention. It is anticipated that these three groups of patients will differ in fundamental ways related to health outcomes that could represent important bias and confounding in this study. For this reason we will calculate propensity scores for each patient, capturing their likelihood to receive either surgery or a prescribed anti-obesity therapy. Using the propensity scores we will ensure comparisons are only made between patients with similar background characteristics (Sturmer et al, 2010). Cox proportional hazard regression will be used to conduct time to event analyses for death, diabetes, cardiovascular disease, fractures and liver disease, adjusting for the propensity score. Patients with no intervention will form the baseline group.

In addition, anonymised, linked Hospital Episode Statistic (HES) data are available for patients in the GPRD and will allow us to look in detail at hospital records for patients who undergo bariatric surgery (e.g. type of surgery, any complication that arise).

Patients who receive orlistat and later have surgery will move from one exposure group to the other, according to current treatment. We anticipate that very few patients will receive orlistat following surgery and any patients who appear to do so will be excluded from the analysis.

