**Amendment**

A number of amendments to this protocol are now sought:

1. Due to funding constraints, it will not be possible to access QRESEARCH data and the study will be restricted to CPRD data only. We do not anticipate major changes to the feasibility of the study, as the current number of patients in the CPRD with bariatric surgery is now >3,000.
2. Following initial data processing it became apparent that matches for bariatric surgery patients, drawn from the population of patients with a BMI >30 were very dissimilar from the surgery patients, mainly because the surgery group tended to have a much higher BMI. Since the guidelines for surgery include a requirement of BMI >=40 in most instances, we propose matches to be drawn from a pool of patients with any measure of BMI >=40 during their registration.
3. For the analysis of weight loss, we intend to measure the effects to a maximum of three years post-intervention, largely driven by the amount of follow up available for surgery patients
4. Following statistical advice from [name], it was decided that mixed effects linear regression should be used to assess changes in weight and BMI over time within each group. We anticipate a non-uniform rate of change over follow up and will model this using splines. The Akaike Information Criterion (AIC) will be used to determine optimal spline knot points. From the final model, weight/BMI and 95% confidence intervals for the study population will be estimated. The rate of change in weight or BMI and 95% confidence intervals will be calculated for each spline component.
5. For all other outcomes, orlistat patients will be censored at the end of follow up, analogous to an intention to treat type analysis, so the long term consequences of the decision to start a course of treatment with orlistat can be measured, regardless of subsequent treatment. As a sensitivity analysis, follow up will be censored at the estimated date treatment was stopped, based on prescribing records.
6. Subgroup analyses according to underlying diabetes and cardiovascular disease status will be carried out, in line with NICE recommendations for research on treatments for obesity. Additionally, where numbers permit, analyses of bariatric surgery patients will be stratified by surgery type.
7. As a clarification, patients who have bariatric surgery and later receive orlistat will be excluded from orlistat analyses only.

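### Objective (a), surgery versus drug treatment, has no planned contrast, and the two comparisons with untreated patients cannot stand in for it

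*Protocol*

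**What the plan says.** The Objectives section names two comparators for surgery: "compare them with a) people receiving pharmaceutical treatment for obesity and b) obese people receiving no treatment". The Lay Summary gives the lack of evidence comparing one treatment with another as a motive for the study, and Specific Aims promises comparison between groups.

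The rest of the Protocol uses a different reference:

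- **Study Type:** the null hypothesis is that "there is no clinical difference in outcomes following bariatric surgery or pharmacological treatment for obesity, compared with receiving no treatment", which leaves out surgery versus drug.
- **Study Design and Study Population:** "Each patient with surgery or orlistat will be matched with up to 5 obese patients without a record of these treatments". The comparison pool is defined by "A record of BMI>30 with neither bariatric surgery nor a prescription for orlistat".
- **Statistical Analysis and Covariates:** for the Cox models, "Patients with no intervention will form the baseline group". On confounding, "we will calculate propensity scores for each patient, capturing their likelihood to receive either surgery or a prescribed anti-obesity therapy". The linear regression of weight and BMI sets each intervention against no intervention.
- **Amendment, item 2:** because "matches for bariatric surgery patients, drawn from the population of patients with a BMI >30 were very dissimilar from the surgery patients", the sponsor changes the pool: "we propose matches to be drawn from a pool of patients with any measure of BMI >=40 during their registration".
- **Amendment, item 4:** weight and BMI move to mixed-effects models of change over time within each group.

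**The concern.** Followed as written, the plan gives a surgery-versus-untreated estimate and an orlistat-versus-untreated estimate, and none for surgery versus orlistat. Objective (a) would go unanswered, or would be answered informally by laying the two hazard ratios side by side.

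The informal route is the real risk. The two untreated groups now appear to have different BMI entry criteria, and the sponsor itself found BMI differences large enough to require changing the surgery pool. A reader who divides one hazard ratio by the other would credit to treatment what may partly reflect which patients were studied.

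**Working it through.** The finding is structural, so the main check sets the sections side by side.

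**1. Is surgery versus drug specified anywhere?**

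| Element | Section | Contrast |
|---|---|---|
| Objective | Objectives | Surgery v drug; surgery v none |
| Null hypothesis | Study Type | Surgery or drug v none |
| Matching | Study Design and Study Population | Treated v untreated, up to 1:5 |
| Power | Sample Size/Power Calculation | Surgery v untreated, 1:5 |
| Cox models, main outcomes | Statistical Analysis and Covariates | Each treatment v none |
| Linear regression, weight/BMI | Statistical Analysis and Covariates | Each treatment v none |
| Mixed models, weight/BMI | Amendment item 4 | Within each group |

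No row after the first contains surgery versus drug. If item 4 replaces only the paired t-tests and the linear regression survives, the reference for weight and BMI is still no intervention.

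**2. Can the ratio of the two hazard ratios serve?** Write b(S,U) for the log hazard ratio of surgery versus untreated and b(O,U) for orlistat versus untreated. Let P40 be the population of the surgery comparison and P30 that of the orlistat comparison.

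- Target in P40: b(S,U; P40) − b(O,U; P40).
- Indirect figure: b(S,U; P40) − b(O,U; P30).
- Indirect minus target: b(O,U; P40) − b(O,U; P30).

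With each comparison correctly adjusted, the discrepancy is zero only if orlistat's effect is the same in both populations. The document gives no figure for this, so the size is unknown. The entry thresholds are 10 BMI units apart (40 − 30). The pools overlap, and item 2 asks only for any qualifying measure during registration, so the actual BMI difference between the groups cannot be derived.

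**3. Does the propensity score help?** The wording allows one score for receiving any treatment, or one score per treatment. The first separates treated from untreated. The second separates surgery from untreated and orlistat from untreated. Neither models surgery against orlistat.

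**4. The plan's own power figure.** The plan states 80% power for 5% versus 3.9% four-year mortality. Inputs are about 2,000 surgery patients, roughly doubled to 4,000, with 20,000 untreated. Two-sided alpha of 0.05 is assumed, as none is given for this figure. With d the difference in proportions and p̄ the pooled proportion:

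power = Φ{ [d − 1.96·√(p̄(1−p̄)(1/n₁+1/n₂))] / √(p₁(1−p₁)/n₁ + p₂(1−p₂)/n₂) }

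- p̄ = (156 + 1,000)/24,000 = 0.0482; the numerator is 0.011 − 1.96 × 0.00371 = 0.00373; the denominator is 0.00343.
- Power = Φ(1.09) = 86.2%.

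The stated 80% is not reproduced but is conservative for those counts. With CPRD alone at 3,000 v 15,000, the same formula gives 74.5% (79.7% by Schoenfeld's formula). All of these are surgery versus untreated and say nothing about objective (a).

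**5. Is a direct contrast feasible?** Take 3,000 surgery patients (Amendment item 1 gives more than 3,000) and 90,000 orlistat patients (22 May 2014 amendment). Assume orlistat patients carry the 5% rate and none are lost to overlap.

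- p̄ = (117 + 4,500)/93,000 = 0.0496; the numerator is 0.011 − 1.96 × 0.00403 = 0.00310; the denominator is 0.00361.
- Power = Φ(0.86) = 80.5%.
- With the original single-database counts, 2,000 v 80,000, it is 62.1%.

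Restricting to overlapping scores would lower these figures. The document gives no overlap figure.

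**The case against.** **Naming a baseline group does not forbid other contrasts.** A three-group Cox model could yield surgery versus orlistat as a difference of coefficients. Specific Aims speaks of comparison between groups, and the statistical analysis plan, not shown, may supply the contrast. This stands so far: the comparison is unspecified, not impossible. But the Protocol is not merely silent. It fixes another reference for the hypothesis, matching and models. The 22 May 2014 amendment also notes that sibutramine versus orlistat had not previously been specified, although both drugs and the outcomes were already in the study. It then gives that comparison its own score, overlap rule and sample size.

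**Four stronger readings are tempting and are not supported.**

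- A reader might infer that every model uses untreated patients as reference. That is untrue of the Cox models between surgery types, the sibutramine-versus-orlistat models and the within-group mixed models.
- A reader might infer that a single combined score is planned and that, with orlistat at 90,000/93,000 = 97% of treated patients, it is in effect an orlistat score that under-adjusts the surgery comparison. The text speaks of scores in the plural and reads equally well as one per treatment. The 97% also joins counts from two amendments and omits the 27,000 sibutramine patients.
- A reader might infer that the untreated groups differ by at least 10 BMI units. Only the thresholds differ by 10.
- A reader might infer that the indirect ratio is confounded by BMI. BMI is a listed covariate, so this is not shown. The supported problem is effect modification across different populations.

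That the orlistat pool stays at BMI >30 is itself an inference. Item 2 discusses only the surgery patients' matches.

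**Conclusion.** The point holds in this form. Objective (a) has no planned contrast: every between-group model that sets surgery or orlistat against another main study group uses no intervention as reference, and the amended weight and BMI models are within group. The two hazard ratios versus untreated do not compare like with like if BMI modifies orlistat's effect. This rests on reading item 2 as leaving the orlistat pool at BMI >30. The propensity score does not fill the gap on either reading.

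No bias can be quantified. The consequence is one of two stated objectives left without an answer, or answered by an unplanned indirect comparison. The data could plausibly support the direct contrast, at about 80% power under the assumptions above and less after overlap restriction. The plan should be changed; the comparisons with untreated patients are not invalidated by this point.

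**What to change.** 1. Add a direct surgery-versus-orlistat Cox analysis for the clinical outcomes and a between-group contrast for weight and BMI. Give it its own propensity score, including index-date BMI, and restrict it to the overlapping score region, as the 22 May 2014 amendment does for sibutramine versus orlistat.
2. State that propensity scores are fitted separately for each contrast.
3. Reconcile two rules for this contrast. Statistical Analysis and Covariates moves orlistat patients who later have surgery into the surgery group. Amendment item 5 follows orlistat patients to the end of follow-up whatever treatment comes later. The estimate depends on which applies.
4. State that the two hazard ratios versus untreated are not to be compared with each other, and say explicitly which BMI pool serves the orlistat matches.
5. If overlap proves too small, restate objective (a) to match the analyses done.

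The cost is one more score model and one more matched analysis on data already held. The downside is lower precision where few orlistat patients have a BMI as high as the surgery group's.

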**Specific Aims**

Rates of the following outcomes will be compared between groups: Mortality, post-operative complications, type 2 diabetes, cardiovascular disease, fractures, cancer, fatty liver, acute liver injury and obstructive sleep apnoea. Changes over time will be compared against baseline and between groups for the following outcomes: weight, body mass index (BMI), lipid profile.

**Background & Rationale**

The prevalence of obesity (BMI>=30) in the UK is currently ~24% and will almost certainly increase over the next five to ten years (Craig, 2006). As a consequence, obesity related health problems such as type-2 diabetes, cardiovascular disease and mobility problems are also common. Combined with psychological stress and social stigma, obesity has a substantial impact on individual quality of life and clinical outcomes (Throsby, 2007).

Various approaches are available to tackle obesity, including diet and exercise, but in many cases surgical or pharmacological treatments may also be used. Randomised trials of surgical and pharmacological interventions for obesity have generally been small and short term, since trials are usually powered to demonstrate efficacy, whilst the reporting of safety outcomes is often incomplete or inconsistent (Papanikolaou 2006, Black 1996). The “real world” safety and effectiveness of these interventions as used in UK secondary/primary care has not been well studied over long periods.

Hospital Episode Statistics were used by Burns et al to evaluate short-term mortality and readmission rates after bariatric surgery in England, comparing gastric banding with bypass in ~7,000 patients (Burns et al, 2010). However, longer term effects and weight loss were not assessed and comparisons with non-surgical treatments were unavailable.

A systematic review of the clinical effectiveness and cost effectiveness of bariatric surgery for obesity was published as an HTA report in 2009 (Picot et al., 2009). One of the studies included, the Swedish Obese Subjects (SOS) prospective cohort study, has been reporting long term outcomes such as weight loss, typical obesity-related clinical outcomes and QoL for up to 10 years in ~2,000 subjects undergoing bariatric surgery compared with a similar number of obese subjects not receiving surgery. They report QoL peaking at 12 months post-surgery, with a subsequent decline and stabilisation at levels above baseline up to 10 years later; a reduction in incident diabetes, hypertriglyceridemia, hyperuricaemia; resolution of type 2 diabetes, hypertension, hypertriglyceridemia and hyperuricaemia; and no difference in incident hypertension or hypercholesterolaemia resolution when comparing surgical with non-surgical treatment (Karlsson et al., 2007).

A further study of the Swedish population compared >1,000 patients receiving bariatric surgery with >5,000 obese non-surgery patients; surgery was followed by a decreased incidence of type 2 diabetes, hyperlipidemia and mortality but no difference for hypertension, angina, MI or stroke (Marsk et al, 2010). Quality of life and weight assessments were not included in this report.

Other relevant studies in non-UK settings have mostly involved small patient numbers, measured a limited range of outcomes or had poor follow up rates, making findings difficult to interpret (Batsis et al, 2010; Picot et al, 2009).

Large scale, comprehensive population-based research measuring the impact of surgery for obesity in the UK, in comparison with other forms of care is therefore lacking. We believe we are ideally placed to answer a number of important questions that will help inform future treatment for obesity.

**Study Type**

This is a hypothesis testing study; throughout the null hypothesis will be that there is no clinical difference in outcomes following bariatric surgery or pharmacological treatment for obesity, compared with receiving no treatment.

**Study Design and Study Population**

A combination of two UK databases offers an excellent opportunity to study the clinical effects of interventions for obesity; the UK General Practice Research Database (GPRD) and QRESEARCH. In combination the GPRD and QRESEARCH contain information from >1100 UK general practices, and have current and historical data for >20 million patients. Continuous patient records include details of all consultations, diagnoses, prescribed medicines and basic demographic data. Patients are representative of the England & Wales population in terms of age, sex and geographical distribution [refs]. Data quality is subject to rigorous checks and audits and >500 peer reviewed studies have been published using GPRD or QRESEARCH data including studies investigating unintended effects of medication (GPRD, 2010; QRESEARCH, 2010). GPRD and QRESEARCH draw information from mutually exclusive practices and are therefore fully complementary.

*3.1 Study Design - Patient population, exposures of interest, inclusion/exclusion criteria*

The cohorts will comprise obese patients registered in the GPRD and QRESEARCH:

- Eligible patients will be those aged 18+ years with at least 12 months research standard registration time in the GPRD or QRESEARCH AND with one of the following exposures recorded by the study start:
  - A record of bariatric surgery with at least 12 months prior registration to ensure incident status (specific type of bariatric surgery used will be determined using data recorded in patient records); OR
  - A first prescription for orlistat with at least 12 months prior registration to ensure incident usage; OR:
  - A record of BMI>30 with neither bariatric surgery nor a prescription for orlistat – these patients will act as the **comparison group**
- The date of surgery or first orlistat prescription will be termed the index date. Each patient with surgery or orlistat will be matched with up to 5 obese patients without a record of these treatments, on age (within 5 years), sex and practice with at least 12 months research standard registration prior to the relevant index date.
- Patients will be followed until the earliest of; an outcome of interest, death, transfer out of the practice or last data collection date.
- As a secondary analysis we will also be able to assess exposure to sibutramine. Whilst the marketing authorisation for sibutramine has been suspended, there is uncertainty over whether marketing may be resumed in the future, and the effects of this drug are therefore still of broad interest.

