**Outcomes**

Outcomes have been chosen as events that are well recorded by GPs as part of routine patient care, regardless of where a diagnosis is made (by the GP or in secondary/tertiary centres). Numerous studies have been published looking at these outcomes using data from the GPRD/QRESEARCH and validity has been shown to be high (GPRD, 2010; QRESEARCH, 2010). The following outcomes will therefore be ascertained for all patients in the cohort:

- Death
- Change in Weight
- Change in BMI
- Diabetes
  - First diagnosis
  - Progression to monotherapy with oral antidiabetic agent
  - Progression to polytherapy with oral antidiabetic agents
  - Progression to insulin therapy
  - Resolution (noted in GP record as patient removal from diabetes QOF register)
- Cardiovascular disease
  - Incident MI
  - Incident stroke
  - Onset of hypertension
  - Onset of angina
  - Improvement of hypertension determined by permanently stopping antihypertensive medication, i.e. at least 6 months without a further prescription
- Osteoporotic Fractures (hip, spine, wrist)
- Acute liver injury as indicated by a diagnostic code or a record of alanine transferase at >3X upper limit of normal in patients without chronic liver disease.
- Fatty liver
- Incident cancer diagnoses
- Obstructive sleep apnoea
- Change in lipid profile

In addition, within the GPRD, Hospital Episode Statistics (HES) data will be available for a large proportion of the cohort. We will therefore be able ascertain post-operative outcomes, including post-operative haemorrhage, post-operative infection, ITU admission, re-admission to hospital and re-operation. Also, within the GPRD, detailed information on acute coronary events will be available via linkages with the Myocardial Ischaemia National Audit Project (MINAP).

The research team has considerable experience in developing algorithms for determining outcomes based on both GPRD and is developing expertise with HES data – algorithms for specific outcomes are available on request.

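### Follow-up starts at a clinical contact for treated patients but at a borrowed date for comparators, so first-diagnosis comparisons may be biased in either direction with no treatment effect

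*Protocol*

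**What the plan says.** Under Study Design and Study Population (3.1), time zero for the treated is the operation or the first orlistat prescription: "The date of surgery or first orlistat prescription will be termed the index date". Comparators are chosen as follows: "Each patient with surgery or orlistat will be matched with up to 5 obese patients without a record of these treatments". The match is on age, sex and practice, "with at least 12 months research standard registration prior to the relevant index date". No consultation, weight, BMI or test near that date is required of them. Item 2 of the Amendment changes the pool for surgery: "we propose matches to be drawn from a pool of patients with any measure of BMI >=40 during their registration". The qualifying measurement can therefore lie far from the index date.

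The end of follow-up is fixed too: "Patients will be followed until the earliest of; an outcome of interest, death, transfer out of the practice or last data collection date".

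The Outcomes section includes diabetes ("First diagnosis"), onset of hypertension, fatty liver and obstructive sleep apnoea. It justifies the list thus: "Outcomes have been chosen as events that are well recorded by GPs as part of routine patient care".

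Statistical Analysis and Covariates relies on a propensity score. The covariates it names are demographic and lifestyle factors, weight, BMI and recorded co-morbidities; contact and testing are not among them. Limitations covers group differences, unrecorded surgery, over-the-counter orlistat and missing data, but not unequal detection.

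**The concern.** A first diagnosis in a GP record needs both the disease and an occasion to look for it. By definition the treated have a clinical contact at time zero, while comparators have only whatever contact falls there by chance. The Outcomes section's assurance concerns the recording of diagnoses once made. It says nothing about whether the groups have the same chance of being tested.

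The imbalance can act in two ways. If the treated patient's extra disease is found before index, it becomes prevalent and leaves the at-risk set, while the same disease in comparators surfaces later as incident events. The treatment then looks protective. If it is found at or just after index, it counts as events in the treated and the treatment looks harmful. Adjusting for recorded disease cannot balance disease not yet recorded.

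The consequences go beyond the hazard ratios. The protocol plans NNT or NNH wherever an effect is seen. Item 1 of the May 2015 amendment applies the relative risks for surgery to 1.4 million people, for every outcome on which surgery appears to have an effect. A spurious protective ratio would become a national count of preventable cases.

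**Working it through.** The protocol states no figure on this point, so there is none to reproduce. The illustration uses diabetes and assumes no treatment effect.

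**Inputs.** Follow-up of 2.4 years for surgery is the mean given under Sample Size/Power Calculation. Four years for orlistat borrows the horizon of the power statement there. All else is assumed: incidence 2% per year; a share u = 2 to 5% undiagnosed at index; background detection of these cases at rate d = 10 to 30% per year (10% for orlistat).

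**Surgery, all undiagnosed disease found before index.**
- Treated risk: S = 1 − exp(−0.02 × 2.4) = 0.0469.
- Comparator risk: C = (1 − u)S + u[1 − exp(−2.4d)].
- u = 2%, d = 10%: C = 0.98 × 0.0469 + 0.02 × 0.2134 = 0.0502; ratio 0.93.
- u = 3%, d = 20%: C = 0.97 × 0.0469 + 0.03 × 0.3812 = 0.0569; ratio 0.82.
- u = 5%, d = 30%: C = 0.95 × 0.0469 + 0.05 × 0.5132 = 0.0702; ratio 0.67.

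**Surgery, only part found before index (u = 3%, d = 20%).** If half is found, the treated risk is (0.97 × 0.0469 + 0.015 × 0.3812)/0.985 = 0.0520, and the ratio is 0.91. If 30% is found, the ratio is 0.95.

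**Orlistat, share f found at the index contact and counted as events.** Over four years S = 1 − exp(−0.08) = 0.0769 and D = 1 − exp(−0.4) = 0.3297. The comparator risk is (1 − u)S + uD; the treated risk is (1 − u)S + u[f + (1 − f)D].
- u = 2%, f = 0.2: 0.0846/0.0819 = 1.03.
- u = 3%, f = 0.3: 0.0905/0.0845 = 1.07.
- u = 5%, f = 0.4: 0.1029/0.0895 = 1.15.

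**Timing sets the sign.** In the middle orlistat case, if the 30% is found before index instead, the treated risk is (0.97 × 0.0769 + 0.021 × 0.3297)/0.991 = 0.0822, and the ratio is 0.97 rather than 1.07.

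**Cross-check with a different model.** Patients move from healthy to undiagnosed to diagnosed, with u = 2 to 8%, diagnosis rate 0.25 to 0.5 per year, f = 10 to 50% and 2.4 years of follow-up. The null rate ratio is about 0.63 to 0.94 if the extra disease is found before index, and about 1.03 to 1.51 if found at or just after it.

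**The planned orlistat sensitivity analysis.** Item 5 of the Amendment censors at the end of treatment. This would not expose the problem, because it concentrates follow-up near index. With u = 3% and f = 0.3, the ratio over one year is 0.0302/0.0221 = 1.37.

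**A three-month lag in both groups (cases diagnosed during the lag removed).**
- Surgery: 0.934 stays 0.934, 0.824 becomes 0.827, and 0.668 becomes 0.675.
- Orlistat: 1.03 becomes 0.99, 1.07 becomes 0.97, and 1.15 becomes 0.95.

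The lag leaves the surgery bias almost untouched because the comparators' undiagnosed cases surface over years. It reverses the orlistat bias because the treated have already been cleared of some undiagnosed disease.

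**The case against.** The strongest reply is that the documents describe no work-up before surgery, no testing at an orlistat consultation and no prevalence of undiagnosed disease. That bias occurs is an inference, and its size and sign rest on assumptions. This stands, and it limits the point in three ways.

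- A reader might infer that these conditions are detected around index only in the treated. They are not: comparators are still diagnosed at the background rate and lack only the extra detection tied to the index contact.
- A reader might infer that the bias must favour surgery and disfavour orlistat. That would need all surgical detection to fall before index and all orlistat detection after it, which no passage establishes. More testing after surgery would offset the surgery bias; tests before a first prescription would reverse the orlistat bias.
- The range 0.67 to 0.93 takes the extreme case in which all undiagnosed disease is found before surgery.

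The reply also notes that practice matching reduces differences in testing and coding, that comparators have had a BMI measured at some time, that the covariate list is open, and that exact covariates and sensitivity analyses commonly belong in a SAP. These have some force: the lack of a named consultation covariate would not be a finding by itself. But the protocol itself fixes time zero and comparator eligibility. Practice matching does not equalise contact between two patients of one practice, and a BMI from any point in registration says nothing about contact near index.

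**Conclusion.** The point holds as a risk of bias built into the stated time-zero rule. It does not show that bias has occurred or which way it runs. First-diagnosis comparisons against untreated patients can depart from 1 with no treatment effect, and no stated safeguard equalises or tests for unequal detection. Under the assumed rates the departure runs from small (0.93 to 0.95, or 1.03) to large enough to be mistaken for a treatment effect (0.67, or 1.15). Only diabetes was modelled; hypertension, fatty liver and sleep apnoea share the mechanism but not necessarily the size. Sleep apnoea is not among the outcomes named for Cox regression, though Specific Aims compares its rate.

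Death is outside this mechanism, and so is the sibutramine-orlistat comparison, where both groups start at a prescription. The point should be addressed before first-diagnosis results feed the NNTs or the 1.4 million projection.

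**What to change.** For first-diagnosis outcomes:

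1. Require comparators to have a GP consultation with a recorded weight or BMI in the 12 months before the matched index date.
2. Add the consultation count in that year to the propensity score.
3. Add a sensitivity analysis restricted to patients in both groups with the relevant test recorded in the year before index, for example glucose or HbA1c for diabetes.
4. Apply NNTs and the 1.4 million projection to these outcomes only where the result holds in that sensitivity analysis.

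Do not adopt a three-month lag as the remedy, for the reasons shown in the calculation.

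The cost is protocol wording and a rerun of the match and the score; the protocol says patient records hold details of all consultations. The comparator pool will shrink. GPRD has more than 1.4 million patients with BMI of at least 30, but the size of the BMI >=40 pool is not stated, so the loss for surgery matches must be counted. Requiring contact may also select comparators who consult more. Some bias can remain: in the cross-check model the null ratio returns to 1.00 if the comparator contact detects as much as the treated patient's index contact, but is still about 1.01 to 1.21 (u = 4 to 8%, disease found at index) if it detects half as much.
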